Patients enrolled onto this trial will be stratified according to the tumor type (radioresistant [soft tissue sarcoma, melanoma, and renal cell carcinoma] versus other non-hematologic tumor histologies). The treatment allocation scheme will be used for randomization to balances these patient factors [10]. Within each stratum, patients will be randomized in a 2:1 ratio to either RFA/PVA and EBRT or EBRT alone. This unequal randomization was chosen given the well-known and documented pain response rates to EBRT, accommodates increased demand for combined modality treatment, allows for a larger sample in the combined modality group to evaluate for potential adverse events, and follows the paradigm established by RTOG 0631. The randomization will be performed by a statistician using stratified permuted block randomization. Allocation concealment technique will be used to prevent selection bias and will be performed on an offsite computer. The recruitment phase will conclude when 52 patients have enrolled in the trial (35 in the RFA/PVA and EBRT arm and 17 in the EBRT alone arm), and it is expected that accrual should be completed over a course of 18 months.

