### Statistical analysis

Based on the reported incidence of complete or partial pain response from the results of the feasibility matched cohort study of RFA/PVA and EBRT [8], with a two-sided *α* = 0.05 and *β* = 0.20 and a study design of 2:1 randomization scheme (RT plus PVA/RFA:RT), the study will be adequately powered with 52 patients (35 in the RT plus PVA/RFA arm and 17 in the RT arm). Assuming a 5% ineligibility rate, a death rate of 15%, and a patient non-compliance rate of 15%, the total sample size required would be 80 patients. No interim analyses with treatment efficacy results are planned. The primary endpoint is complete or partial pain response at 3 months after randomization, and all eligible, randomized patients will be included in the analysis regardless of treatment compliance (intent-to-treat analysis). Descriptive statistics of the actual change scores, mean change scores, and standard deviations will also be reported. For analysis of the secondary pain response endpoints (rapidity of pain response and duration of pain response), the median time to each outcome variable will be estimated using the Kaplan-Meier approach, the stratified log-rank test will be used to test for statistically significant differences with an α = 0.025, and the Cox proportional hazards regression model will be used to determine hazard ratios and 95% confidence intervals for the treatment differences. Moreover, unadjusted ratios and adjusted ratios for radiosensitive vs. radioresistant histology will be computed. The incidence of adverse events will be reported according to CTCAE v5.0, and differences in the rates at 3 months between the two treatment arms will be tested using the two-sided chi-square test at the 0.05 significance level. To analyze differences in QOL, global pain, and health utility, changes in FACT-G, BPI, and EQ-5D will be described with longitudinal data analysis. The mean differences will be compared across the treatment arms using the two sample *t* test at the 0.025 significance level. The relationship between treatment response and QOL will also be analyzed using the two sample *t* test at the 0.025 significance level.

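### The one stated between-arm test of adverse events, a chi-square at 0.05, suits sparse 35:17 data poorly; a risk difference with an interval would say more at almost no cost

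*Protocol article*

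**What the plan says.** All the analysis text on safety is in one sentence of the Statistical analysis section of the protocol article. It has two halves. The descriptive half reads: "The incidence of adverse events will be reported according to CTCAE v5.0". The comparative half reads: "differences in the rates at 3 months between the two treatment arms will be tested using the two-sided chi-square test", at a level of 0.05. The article does not say whether a continuity correction applies, and it names no other comparison of adverse events between arms.

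The same section sizes the trial for the pain endpoint at "52 patients (35 in the RT plus PVA/RFA arm and 17 in the RT arm"), raised to 80 in total for ineligibility, death and non-compliance. Under Recruitment and randomization, one of the reasons given for 2:1 allocation is that it "allows for a larger sample in the combined modality group to evaluate for potential adverse events".

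Elsewhere, the Data management section provides for committee review every 3 months. The section on ethics, information and safety provides for twice-yearly reports of adverse event frequency and severity, and for grading and attribution of unexpected events. These are oversight and description, not comparisons between arms.

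**The concern.** Needle placement, ablation and cement injection happen only in the experimental arm. An event specific to the procedure will therefore have a control rate at or near zero. That produces sparse tables with an empty or nearly empty EBRT cell, in the smaller of two unequal arms, where a chi-square approximation is least reliable.

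Two things are at stake. The test may give no signal for an excess that a reader would want to know about. It may also give a nominal signal against EBRT alone on very few events. In both cases a bare p-value tells the reader nothing about how large an excess the data still allow. In the same section, hazard ratios for the secondary pain endpoints are to carry 95% confidence intervals, while the adverse event comparison is given a test only.

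**Working it through.** **Inputs from the article.** Arm sizes 35 and 17; total after inflation 80, which is about 53:27 at 2:1; two-sided chi-square test at 0.05. The article gives no adverse event rates, so every rate below is an assumption, shown over a range. The critical counts need no assumed rate.

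**The plan's own figure.** The inputs are response rates of 93.3% vs 59.9% (Background), two-sided 0.05, 80% power and a 2:1 ratio. The pooled proportion is (2 × 0.933 + 0.599)/3 = 0.8217. The control arm needs

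[1.96 × √(1.5 × 0.8217 × 0.1783) + 0.8416 × √(0.599 × 0.401 + 0.933 × 0.067/2)]² / 0.334² = 16.5, so 17.

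That gives 17 + 34 = 51, against the stated 52. The inflation 52/(1 − 0.35) = 80 also agrees. The arm sizes thus come from efficacy alone.

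**Expected counts.** With t patients having the event, the expected EBRT count is t × 17/52. For t = 15 this is 4.90 and for t = 16 it is 5.23. Any event affecting 15 or fewer patients in total falls below the usual minimum of 5.

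**Critical counts, no events in the other arm.** The uncorrected statistic is χ² = N(ad − bc)² / (product of the four margins).

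| Table (RFA/PVA vs EBRT) | χ² | Uncorrected p | Yates p | Fisher p |
|---|---|---|---|---|
| 6/35 vs 0/17 | 52 × (6 × 17)² / (35 × 17 × 6 × 46) = 3.29 | 0.070 | 0.18 | 0.16 |
| 7/35 vs 0/17 | 52 × (7 × 17)² / (35 × 17 × 7 × 45) = 3.93 | 0.047 | 0.12 | 0.081 |
| 0/35 vs 2/17 | 52 × (2 × 35)² / (35 × 17 × 2 × 50) = 4.28 | 0.039 | 0.19 | 0.10 |

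So the uncorrected test needs 7/35 (20%) on RFA/PVA but 2/17 (12%) on EBRT. Fisher's test needs 8 and 3; Yates needs 10 and 4. At 53:27 the uncorrected thresholds are again 7 and 2.

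**Power for excess harm on RFA/PVA.** All tables were enumerated and binomial probabilities summed where p < 0.05. With a zero control rate this is just P(X ≥ 7); for X ~ Bin(35, 0.10) it is 5.5%.

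| True rates, RFA/PVA vs EBRT | 35:17 uncorrected | 35:17 Fisher | 53:27 uncorrected |
|---|---|---|---|
| 10% vs 0% | 5.5% | 2.0% | 27.7% |
| 15% vs 0% | 26.5% | 14.4% | 70.0% |
| 20% vs 0% | 56.7% | 40.1% | 92.7% |
| 20% vs 5% | 26.6% | 18.1% | 45.2% |
| 30% vs 10% | 35.4% | 27.7% | 55.2% |

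The mirror image, 10% on EBRT vs 0% on RFA/PVA, has power 1 − 0.9¹⁷ − 17 × 0.1 × 0.9¹⁶ = 51.8% at 35:17, against 5.5% in the other direction.

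**Where the imbalance stops.** With equal true rates at 35:17, false signals against RFA/PVA and against EBRT are 0.06% and 3.75% at a rate of 5%, and 2.1% and 2.8% at a rate of 20%. The imbalance is a rare-event effect.

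**What an interval shows.** For 6/35 vs 0/17 the Newcombe 95% interval for the difference runs from −3.4 to +32.7 points. The exact 95% interval for 6/35 alone is 6.6% to 33.6%. If 0/35 had the event, the one-sided 95% upper bound is 1 − 0.05^(1/35) = 8.2%.

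**The case against.** A reader might infer that the plan would take a non-significant test as proof of no added harm. The article does not say so. It sets no safety hypothesis or decision rule, and it also promises incidence by CTCAE, so 6/35 vs 0/17 would be visible in the report. That objection stands.

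A reader might also infer that the test misses most relevant harms. The article names no relevant harm and gives no rate, so this cannot be shown. At 35:17, power reaches 80% at about 25% vs 0%, and with 80 patients analysed it is good for large excesses. Nor does the 2:1 rationale contradict the test: a larger RFA/PVA arm does improve estimation within that arm, and no powered comparison is promised.

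Three further points stand. The two-event signal against EBRT depends on the uncorrected form, which the article does not specify; it disappears with Yates or Fisher. Low power for harms follows from a trial sized for efficacy, and no choice of test cures it. Intervals, event categories and a fallback for small counts may be in an analysis plan that is not shown, so their absence here is not an error.

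What is left concerns what the article does fix. It names one comparative method for adverse events, and that method fits sparse data at this ratio badly.

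**Conclusion.** The point holds as an inexpensive improvement to a stated method; it does not affect the primary endpoint. Three facts rest only on the article's arm sizes: expected EBRT counts below 5 for up to 15 events in total, uncorrected critical counts of 7/35 and 2/17, and Fisher p-values of 0.081 and 0.10 at those counts. The critical counts further assume no continuity correction. The power figures also rest on assumed event rates: for procedure-specific harms of 10% to 15% against none, 5.5% to 26.5% at 35:17 and 27.7% to 70.0% at 53:27. The imbalance between directions is strong near 5% and largely gone at about 20% or more. On these figures a non-significant result would carry little information about excess harm from an uncommon event.

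**What to change.** Replace the comparative half of the adverse event sentence with wording such as: *Adverse event proportions at 3 months will be compared as a risk difference with a 95% score-based confidence interval. The incidence of procedure-related events in the RFA/PVA arm will be reported with an exact 95% upper bound. Any p-value will come from an exact test. A non-significant difference will not be taken as evidence of no added harm.* The descriptive CTCAE reporting stays as it is.

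This is a change of wording, with no new data or patients. It has three costs. The exact test guards against false signals on sparse counts but is less powerful than the chi-square (10% vs 0%: 2.0% against 5.5%; 20% vs 0%: 40% against 57%), so the p-value should be secondary or left out. The interval neither raises power nor removes the asymmetry; it only makes the uncertainty visible. Safety statements will read as less certain, which is what data of this size support.

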**Table 1 Tab1:** Study parameter table

Assessments	Pre-treatment	1 month from randomization	Follow-up: At 3, 6, 12, 24 months from randomization
History/physical	Within 2 weeks prior to registration		X
Performance status	Baseline		X
Neurological exam	Within 1 week prior to registration		X
Imaging of the spine (CT scan/bone scan is allowed, MRI preferred)	Within 6 weeks prior to registration		X
Numerical rating pain scale and documentation of patient’s pain medication^a^	Within 1 week prior to registration	(On the day of treatment) (At home: Daily with cumulative weekly measurements at 1, 2, and 3 weeks; bring to clinic at 1 month) In clinic at 1 month	X
FACT-G (FA), BPI (QL), EQ-5D (HP)	Baseline		At 3, 6, 12, and 24 months from randomization
Adverse event evaluation		X	X

^a^NRPS at 3 months is required for analysis of the primary endpoint

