### Assessment of the primary and secondary endpoints

The primary endpoint for this trial is pain response, defined as complete or partial pain relief, as measured using the NRPS at 3 months (post-treatment pain score of 0 or at least 3 NRPS points). The NRPS is a widely utilized assessment of pain intensity in oncologic clinics and has demonstrated reliability in studies of small sample sizes and in settings where repeated measurements are obtained to monitor changes in pain intensity over time [11]. Using this scale, complete pain relief is defined as a pain score of 0 with no increase in narcotic pain medication, and partial pain relief is defined as a reduction in numerical pain score of at least 2 points at the index site with no increase in pain medication.

Secondary pain response endpoints include the rapidity of pain response, as defined as the time from study entry to complete or partial pain relief, and duration of pain response, as defined as the time from complete or partial pain relief to pain worsening (≥ 3 NRPS points). To assess these outcomes, patients will complete the NRPS for each treatment site at the baseline clinic visit (on the day of treatment) and daily at home with weekly measurements at 1, 2, and 3 weeks after randomization in addition to a diary of their pain medication use and any side effects they experience related to the treatment. One month after treatment, patients will complete the NRPS, and at the clinic visit, the research team will consolidate the patients’ pain level scores, pain medications, and document adverse events. Imaging of the treated spine will be obtained at baseline and at 3, 6, 12, and 24 months after randomization to assess the response to treatment as well as subacute or long-term change of the vertebral bone.

The study hypothesis is that given the potential benefit of combined modality treatment in providing rapid and durable pain relief, QOL will improve after RFA/PVA and EBRT. Therefore, a number of QOL outcomes will also be prospectively collected in this study, including QOL, as measured by the Functional Assessment of Cancer Therapy (FACT-G) [12]; patient perception of pain, as measured by the Brief Pain Inventory (BPI) [13]; and health utilities, as measured by the EuroQol (EQ-5D) [14] at 3, 6, 12, and 24 months post-study randomization.

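### The t test on change in FACT-G, BPI and EQ-5D omits baseline and histology as covariates, and its unexplained 0.025 level fits two tests rather than three instruments

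*Protocol article*

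**What the plan says.** The Statistical analysis section of the protocol article treats the three questionnaires in two steps. First, "changes in FACT-G, BPI, and EQ-5D will be described with longitudinal data analysis". Then comes the inference: "The mean differences will be compared across the treatment arms using the two sample" *t* "test at the 0.025 significance level". A further comparison follows at the same level: "The relationship between treatment response and QOL will also be analyzed using the two sample" *t* test. That one relates response to QOL and does not compare the arms.

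The section names no covariate for the t test, does not say which visit or visits it covers, and gives no reason for 0.025. For the two pain time endpoints, by contrast, it plans a stratified log-rank test, also at 0.025, and ratios adjusted for histology.

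The data for a better analysis are already collected. Table 1 schedules all three instruments at baseline. The section on endpoint assessment adds follow-up "at 3, 6, 12, and 24 months post-study randomization". The section on randomization states: "Patients enrolled onto this trial will be stratified according to the tumor type", meaning radioresistant against other histologies.

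**The concern.** The protocol does not leave the QOL comparison open. It names the test and the level, so both can be judged as written.

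Two features look weak. First, a t test on change uses baseline only by subtraction. That is less precise than adjusting for it, and part of any chance baseline difference between the arms stays in the estimate. The stratification factor plays no role, although the same section uses it for the time endpoints. Second, 0.025 is half of 0.05, which suits a pair of tests such as the two pain time endpoints. Here there are three instruments.

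At stake is the QOL part of the trial. The article states a hypothesis that QOL improves after combined treatment and lists pain impact, health utility and QOL among its secondary objectives. With a control arm of about 17 analysable patients, little precision can be spared.

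**Working it through.** **Inputs from the protocol article**
- Analysable patients: 35 and 17 (Statistical analysis).
- Three instruments, measured at baseline and at four follow-up visits (Table 1; endpoint assessment section).
- Level per test: 0.025 (Statistical analysis). Sidedness is not stated; I take it as two-sided.

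**Assumed, because the article gives no figure**
- Correlation rho between baseline and follow-up score: 0.3 to 0.7.
- Correlation between test statistics: 0 to 0.9.

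**1. The plan's own figure.** The article gives no power or standard deviation for QOL, so the only sample size to reproduce is that for the primary endpoint. With response rates of 59.9% and 93.3%, two-sided 0.05, power 0.80 and allocation k = 2, the pooled rate is (0.599 + 2 × 0.933)/3 = 0.822, and

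n(control) = [1.960 × √(0.822 × 0.178 × 1.5) + 0.842 × √(0.599 × 0.401 + 0.933 × 0.067/2)]² / 0.334² ≈ 16.5, rounded up to 17.

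That gives 17 + 34 = 51, against the stated 52. Power at 17 and 35 is 81.5%. The stated total is 52/(1 − 0.35) = 80. So 35 and 17 are the numbers expected after losses, and they are the right scale for judging QOL.

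**2. Precision.** With equal standard deviation s at both times:
- variance of a change score: 2s²(1 − rho)
- variance after baseline adjustment: s²(1 − rho²)
- ratio, adjusted to change score: (1 + rho)/2

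| rho | ratio | extra patients the t test needs for equal precision |
|---|---|---|
| 0.3 | 0.65 | 1/0.65 − 1 = 54% |
| 0.5 | 0.75 | 1/0.75 − 1 = 33% |
| 0.7 | 0.85 | 1/0.85 − 1 = 18% |

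The two variances differ by s²(1 − rho)², which is positive for any rho below 1, so the direction does not depend on the assumed value. These ratios are for one visit with complete data.

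**3. Chance baseline imbalance.** With 35 and 17 patients, the baseline difference between arms has standard deviation √(1/35 + 1/17) = 0.30 baseline SD. A change score carries −(1 − rho) times that difference into the result: half of it at rho 0.5, and 0.3 of it at rho 0.7.

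**4. Error rate at 0.025 per test.** For m independent tests it is 1 − 0.975^m:
- m = 2: 4.9%
- m = 3 (one test per instrument): 7.3%
- m = 12 (three instruments at four visits): 26.2%

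For correlated tests, simulation of multivariate normal statistics (300,000 draws) gives:

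| correlation | 3 tests | 12 tests (same correlation between instruments and between visits) |
|---|---|---|
| 0.5 | 6.5% | 20.4% |
| 0.7 | 5.8% | 15.0% |
| 0.8 | 5.1% | not run |
| 0.9 | 4.4% | 8.3% |

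The response-versus-QOL test is not counted, since it does not compare the arms.

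**The case against.** The case against has several parts, and much of it stands.

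- A reader might infer that baseline is ignored. It is not: changes are analysed, so baseline is subtracted, and only the fraction in step 3 of any imbalance remains.
- A reader might infer that repeated measures are ignored. Longitudinal analysis is named, though the article attaches it to description and attaches the test of the arms to the t test.
- A reader might infer twelve tests, or that each test uses only the patients present at that visit. The article says when QOL is collected. It does not say that the t test is run at every visit or how missing scores are handled. Both are commonly settled in an analysis plan, so neither is a finding.
- Family-wise control is not promised for QOL. The endpoints are secondary, and the primary test at two-sided 0.05 is untouched.
- An unadjusted comparison after stratified randomization remains valid and tends to be conservative. I have put no figure on the gain from adding the stratum.
- The sample size was not based on QOL, so the precision loss has no planned power to be set against.

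What is left is narrower. The article does fix the test and the level; the test is less efficient than one using data already in hand; and 0.025 is unexplained for three instruments.

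**Conclusion.** The point holds as a matter of efficiency and clarity, not of validity. The t test on change gives away precision whenever rho is below 1. The size depends on rho, which the article does not give: the adjusted variance is 0.65 to 0.85 of the change-score variance for rho from 0.3 to 0.7.

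The multiplicity part is secondary and more debatable. On the narrowest count, one test per instrument, the error is 7.3% if the tests are independent, about 5% at a correlation near 0.8, and below 5% at 0.9. The stronger claim that it certainly exceeds 5%, or reaches 26%, is not supported: 26% needs independence and testing at all four visits, and the article states neither. Nor does any stated guarantee fail, because none is made.

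The change is worth making because it costs little and bears on a stated QOL hypothesis. It does not affect the primary conclusion.

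**What to change.** Let the longitudinal analysis supply the between-arm test. Fit one mixed model for repeated measures per instrument, with change from baseline as outcome and arm, visit, arm-by-visit, baseline score and histology stratum as terms. Name the 3-month contrast, which matches the time of the primary endpoint, as the tested comparison. Report the other visits as estimates with confidence intervals. Interpret the later visits with care: deaths truncate the scores, and the mixed model does not cure that.

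Then state what 0.025 is meant to protect. If 5% across the three instruments is intended, use Holm at a total of 0.05. If not, label the QOL tests as not controlled for multiplicity.

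The cost is wording only, since baseline scores, all visits and the stratum are already collected. Under Holm the first step is 0.05/3 = 0.0167 instead of 0.025, a small loss for the smallest p-value. Adding the stratum and baseline at a single visit takes the error degrees of freedom from 52 − 2 = 50 to 52 − 4 = 48, which is negligible.

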Radiofrequency ablation, with or without percutaneous vertebral augmentation (RFA/PVA), has been used to treat pathologic fractures associated with spine metastasis with high rates of initial pain response [6]. Using this technique, disease in the central portion of the vertebral body, or that approaching the posterior elements, is first treated with lethal thermal radiofrequency (RF) energy, and the remaining bone is reinforced with cement to provide stability. Retrospective series have demonstrated significant early pain response and reduction in narcotic use as early as 1 week post-treatment [7]. Investigation into the benefits of a multi-modality approach is warranted, as RFA offers rapid pain relief but has limited oncologic effect by not addressing the entirety of the vertebral metastatic disease, especially in lesions in paraspinal locations and with disease in posterior elements. A small, non-randomized feasibility study of RFA and EBRT forms the basis of the combined modality approach investigated in this trial. In this study of 15 patients with bone metastasis and a pre-treatment pain score of at least 5 treated with RFA and EBRT (20 Gy in 5 fractions) matched to patients treated with EBRT alone, higher rates of complete pain response (53.3 vs. 16.6%, *p* = 0.027) and overall pain response (93.3 vs. 59.9%, *p* = 0.048) were observed [8]. This study was limited by the RF technology available at the time, lack of PVA in at-risk patients, as well as small sample size; therefore, further randomized prospective evidence is needed to characterize the benefits of modern combined modality techniques.

The primary objective of this randomized, controlled trial is to determine whether RFA/PVA in addition to EBRT improves pain control compared to EBRT alone for patients with spine metastasis. Secondary objectives include determining whether combined modality treatment improves the rapidity of pain response, duration of pain response, patient reported pain impact, health utility, and overall quality of life (QOL).

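### The planned t test of treatment response against QOL can pick up an arm effect as a response effect; a regression that includes arm would separate them

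*Protocol article*

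**What the plan says.** The Statistical analysis section of the protocol article plans two separate QOL tests. The first is between arms: "The mean differences will be compared across the treatment arms using the two sample" t test. The second concerns response: "The relationship between treatment response and QOL will also be analyzed using the two sample" t test, again a "test at the 0.025 significance level". No covariate, stratum or split by arm is named for the second test.

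The only response that the article defines is pain response, based on the patient's own NRPS score and, for the primary endpoint, taken at 3 months. The Background gives the rates from the feasibility study on which the sample size rests: "overall pain response (93.3 vs. 59.9" per cent. Under Assessment of the primary and secondary endpoints, the hypothesis is that "given the potential benefit of combined modality treatment in providing rapid and durable pain relief, QOL will improve after RFA/PVA and EBRT".

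The article uses the term QOL in two ways. The endpoint section applies it as an umbrella for FACT-G, BPI and EQ-5D, and describes BPI as "patient perception of pain, as measured by the Brief Pain Inventory (BPI"). The Statistical analysis section pairs QOL with FACT-G, global pain with BPI, and health utility with EQ-5D.

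**The concern.** A two-sample t test takes two groups and no covariates. With response as the grouping factor, the groups are responders and non-responders. Patients are not randomized to these groups, and the design expects arm to drive membership strongly. The article also expects arm to improve QOL. It credits this to relief that is rapid and durable, and a single yes/no response at 3 months captures neither feature fully. Arm is therefore a potential common cause of both variables, and a pooled comparison cannot tell a response-QOL link from an arm-QOL link.

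What is at stake is the interpretation of a supporting analysis. A significant result would naturally be read as showing that patients whose pain responds have better QOL, although the same result can arise with no such link within either arm. A second, conditional issue is that if QOL here includes BPI, one patient-reported pain scale is being tested against a response defined by another.

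**Working it through.** **Inputs.** Response 93.3% (RFA/PVA plus EBRT) and 59.9% (EBRT alone), from the Background. Evaluable patients 35 and 17, and alpha 0.025 for QOL tests, from Statistical analysis. The sidedness of 0.025 is not stated and is taken as two-sided. The article gives no QOL effect or SD, so arm effects are assumed over a range of 0 to 1.0 SD.

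**The plan's own figure.** The sample size is set "with a two-sided *α* = 0.05 and *β* = 0.20" with 2:1 allocation. With pooled variance, r = 2 and p̄ = (0.599 + 2 × 0.933)/3 = 0.822:

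n(EBRT) = [1.96 √(1.5 × 0.822 × 0.178) + 0.842 √(0.599 × 0.401 + 0.933 × 0.067/2)]² / (0.933 − 0.599)² ≈ 16.5, rounded up to 17.

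This gives 17 + 34 = 51, against 52 stated. Power at 17 and 35 is 0.815 (0.801 by exact calculation for Fisher's test). Also 52/(1 − 0.35) = 80, as stated. The two response rates are therefore the design rates.

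**Make-up of the groups compared.**

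| | RFA/PVA + EBRT | EBRT | Total | RFA/PVA share |
|---|---|---|---|---|
| Responders | 35 × 0.933 = 32.7 | 17 × 0.599 = 10.2 | 42.8 | 76% |
| Non-responders | 2.3 | 6.8 | 9.2 | 26% |

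Separate t tests by arm would leave about 2.3 non-responders in one arm and 6.8 in the other, so pooling is the workable reading.

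**Share of an arm effect that leaks in.** If arm shifts QOL by d SD and response has no relation to QOL within arm, the expected responder-minus-non-responder difference is d × (0.762 − 0.256) = 0.506 d. At d = 0.5 this is 0.25 SD; the simulated mean difference was 0.26 SD.

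**Rejection rates.** QOL was simulated as normal with unit SD plus d for RFA/PVA patients, independent of response within arm, at 35:17 and two-sided 0.025. The model with arm is a linear regression on arm and response. Results are from 15,000 trials per case, except at 0.3 SD, where separate runs gave 3.8% to 4.2%.

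| Assumed arm effect (SD) | Pooled t test | Model with arm |
|---|---|---|
| 0 | 2.6% | 2.7% |
| 0.2 | 3.2% | 2.5% |
| 0.3 | about 4% | 2.3–2.9% |
| 0.5 | 6.3% | 2.4% |
| 0.8 | 11.3% | 2.4% |
| 1.0 | 16.9% | 2.6% |

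Repeat runs gave 6.0–6.3%, 11.3–11.7% and 16.5–17.1% for the pooled test at the last three effects. With arm in the model, rejection was 2.3–2.9% throughout.

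**BPI, if it is included.** With no arm effect on BPI and an assumed within-arm correlation of 0.3, 0.5 or 0.7 between BPI and the NRPS pain behind response, the pooled test rejects in 15%, 41% and 76% of trials. With arm in the model the figures are 17%, 49% and 84% (8,000 trials each). Adjusting for arm therefore does not remove this overlap.

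**The case against.** The strongest reply is that equal mean QOL in responders and non-responders is a proper null for a relationship between the two, and the t test is a valid test of it. If arm drives both, a marginal association exists and rejecting is correct. This stands. A reader might infer that the test has an inflated type I error, but the article states no within-arm or causal hypothesis. The excess rejection is measured against the conditional question, which is the more useful one but not the one written down.

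The arm effects are also assumptions. Much of any QOL gain may run through pain response, and to that extent the association is genuine. This stands too, and it limits the size of the point. Larger rates, 8.2%, 17.4% and 25.4% at 0.5, 0.8 and 1.0 SD, arise at 53:27. That treats all 80 enrolled patients as evaluable, whereas the plan expects 52.

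A reader might further infer that the BPI test is bound to be significant. The documents do not support that. The Statistical analysis section separates BPI from QOL, so BPI may not be in this analysis at all. Rejection rates of 90–99% at correlations of 0.6–0.8 require BPI also to carry an arm shift of about 1.25 SD times the correlation; without one they are roughly 58–89%.

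Nor does the article say that it will rest a claim about pain relief and QOL on this test. The QOL hypothesis is between arms and has its own test, and the response-QOL relationship is not among the listed secondary objectives.

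Finally, a condensed article may leave covariates to the full plan. That carries less weight here. The article names a method that admits no covariates, while the same section specifies a stratified log-rank test and histology-adjusted ratios for the time-to-event endpoints.

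**Conclusion.** The point holds as a limited one. The stated method tests a marginal association that carries about half (0.51) of any arm effect on QOL not acting through 3-month response. Its size depends on that unknown effect: negligible at 0.2 SD (about 3% against 2.5%), small at 0.3 SD (about 4%), and material at 0.5 to 1.0 SD (about 6% to 17%). The conclusion rests on the design response rates, 35:17 evaluable patients, a two-sided 0.025 level, treatment response meaning 3-month pain response, and responders and non-responders being pooled over arms. The last two are readings of the text, not its words.

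The BPI issue is conditional on the umbrella meaning of QOL. If that meaning applies, response and outcome overlap in content, and a significant BPI result says little about wider QOL. The primary endpoint and the between-arm QOL comparison are unaffected.

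**What to change.** Replace the t test with a linear regression of the 3-month FACT-G score, and likewise the EQ-5D score, on 3-month pain response, treatment arm, baseline score and tumor-type stratum. Report the response coefficient with its confidence interval and call it an association, since adjustment for arm does not make it causal. State which scales QOL covers in this sentence. If BPI is covered, report it as convergent evidence on pain and not as a test of the response-QOL relationship.

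The change is one sentence of analysis wording, and every variable is already collected. The cost is some precision. At the expected counts the squared correlation between response and arm is (32.655 × 6.817 − 2.345 × 10.183)² / (35 × 17 × 42.838 × 9.162) = 0.17. Adding arm therefore widens the standard error of the response coefficient by a factor of about √(1/(1 − 0.17)) = 1.10, other things equal. With only about 9 non-responders expected among 52 patients, about 2 of them in the RFA/PVA arm, the estimate will be imprecise by any method, which is a further reason to report an interval.
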